**Statistical analysis**

This present exploratory study will investigate whether gold ions have a clinical role in treating KOA. Based on preclinical evidence, we estimated medium effect size (Cohen’s d = 0.5), and with a power of 80% and a significant level at 0.05, a sample size calculation estimated a total sample of 27 subjects will be needed in group 1. A total of 30 subjects will be included to account for possible drop-out.

The clinical outcome measures analysis will be performed using the Stata software, version 16.0 (StataCorp.) ANOVA will be used for the analysis of repeated measures of pain, the pain diary, and QST parameters. Wilcoxon test will be used for all other measurements.

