**Expected outcome**

For the included 30 patients we expect a difference of 0.5 SD in the primary outcome, the patient-reported pain, and the function questionnaire WOMAC. For the total sample of included and excluded patients, we expect more than 70% to report a benefit of treatment on a global outcome measure.

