**Study goals and objectives**

The purpose of this study is to investigate if specific effects can be obtained by modulating selectively macrophages and mast cells in the osteoarthritic knee joint as assessed by mechanistic pain assessment tools (quantitative sensory testing), blood and synovial fluid analysis, and clinical pain ratings in patients with painful knee osteoarthritis.

Hypothesis: Modulating macrophages and mast cells by gold microparticles injected into the osteoarthritic knee joint will modulate inflammation specifically, inhibit pain sensitisation and provide pain relief to patients with knee OA.

The aim of this study is to use gold particles as a model compound to modulate specifically and selectively the function of macrophages and mast cells and investigate how this modulates pain and pain sensitization, clinical outcome, and proteomic markers in synovial fluid and serum.

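### The group 1 sample size of 27 matches a one-sided 5% paired test, but no one-sided test is declared and ANOVA is named; on a two-sided before-after test of the change, power is 71% (27 patients) to 75% (30)

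*Protocol*

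**What the plan says.** The sample-size paragraph (Protocol, Statistical analysis) gives the effect as "we estimated medium effect size (Cohen’s d = 0.5", and continues "with a power of 80% and a significant level at 0.05, a sample size calculation estimated a total sample of 27 subjects". Enrolment is set at 30 to allow for drop-out, with no drop-out rate stated. Sidedness is not mentioned here or elsewhere; the level is given only as "a significant level at 0.05".

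The summary (Expected outcome) words the effect as "we expect a difference of 0.5 SD in the primary outcome", the outcome being WOMAC. Neither place says whether the SD is that of the change or that of the score.

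The same Statistical analysis section assigns ANOVA to repeated pain measures, the pain diary and the QST parameters, and adds "Wilcoxon test will be used for all other measurements". QST is measured twice, before treatment and at 8 weeks; WOMAC is measured at baseline, 8 weeks and 2 years. There is no placebo control (Study shortcomings), so the group 1 comparison is before-after. The hypothesis is worded directionally, "inhibit pain sensitisation and provide pain relief to patients with knee OA" (Study goals and objectives), but that sentence does not specify a test.

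**The concern.** An unqualified 5% level is normally read as two-sided, and on that reading a before-after comparison at d = 0.5 needs more than 27 patients. The smaller number appears when the whole 5% is put in one tail. If that is how 27 was obtained, the sample size and the analysis rest on different tests: a one-sided calculation, followed by an ANOVA that cannot be one-sided in the usual sense.

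At stake is how a null result is read. With 80% power the planned effect is missed 20% of the time; with 71% it is missed 29% of the time. A non-significant WOMAC or QST result would then be judged against more power than the planned analysis has.

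**Working it through.** **Inputs.** d = 0.5, level 0.05, power 80%, n = 27, enrolment 30 (Statistical analysis); single group, no control (Study shortcomings). Sidedness, the test used for the calculation, the SD behind d and the before-after correlation are not given.

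**Method.** Paired t-test on the change, with n − 1 degrees of freedom and non-centrality d√n. Power is the probability that a non-central t variable exceeds the critical value t(1 − α/s, n − 1), where s is the number of sides (for s = 2 the negligible opposite tail is added).

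**1. Reproducing the plan's figure (one-sided 5%, d on the SD of the change).**
- n = 26: non-centrality 0.5 × √26 = 2.55, critical t = 1.708, power 79.8%.
- n = 27: non-centrality 0.5 × √27 = 2.60, critical t = 1.706, power 81.2%.

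So 27 is the smallest n that reaches 80%, exactly as stated.

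**2. The same inputs, two-sided 5%.**

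| n | non-centrality | critical t | power |
|---|---|---|---|
| 27 | 2.60 | 2.056 | 70.6% |
| 30 | 2.74 | 2.045 | 75.4% |
| 33 | 2.87 | 2.037 | 79.5% |
| 34 | 2.92 | 2.035 | 80.8% |

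The smallest n is 34. The effect detectable with 80% power is d = 0.56 at n = 27 and 0.53 at n = 30.

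**3. The named analyses.** With two time points, repeated-measures ANOVA is the two-sided paired t-test (F = t²), so step 2 applies directly to QST: 70.6% at 27. For a two-sided Wilcoxon signed-rank test on normal data, the large-sample relative efficiency 3/π gives about 68% at 27 and 73% at 30, slightly below the t-test.

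**4. Readings on which a two-sided test comes close to 27.**

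*d on the SD of the score.* With before-after correlation ρ (assumed, not stated), the effect on the change scale is 0.5/√(2(1 − ρ)).

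| ρ | effect on the change scale | two-sided power, n = 27 |
|---|---|---|
| 0.3 | 0.423 | 56% |
| 0.5 | 0.500 | 71% |
| 0.6 | 0.559 | 79.8% |
| 0.7 | 0.645 | 90% |

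At ρ = 0.6 the required n is 28; at ρ = 0.61 it is 27.

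*Three-time-point F-test.* With f = 0.25, ρ = 0.5 and sphericity (all assumed), the non-centrality is f² × 3n/(1 − ρ) = 0.0625 × 81/0.5 = 10.1 at n = 27. Power is 79.6%, and 28 are needed. However, f = 0.25 corresponds to d = 0.5 only for two means. For three means spanning 0.5 SD, f is the SD of the means: 0.20 for (0, 0.25, 0.5) and 0.24 for (0, 0.5, 0.5). Power at 27 is then 61% and 74%.

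**The case against.** The strongest reply is that the protocol never says two-sided. Its figures fit a standard one-sided calculation exactly, and its hypothesis has a direction. On this view the reviewer supplies the two-sidedness and then finds a conflict with it; what is really missing is a detail of the kind a statistical analysis plan often settles. Two-sided routes to about 27 also exist: d on the score SD with a correlation near 0.6, or a three-time-point F-test with f = 0.25. On either of these, 30 completers would have about 84% power.

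Much of this stands. A reader might infer that the stated 80% is simply wrong, or that 27 can give 80% power only with a one-sided test. The protocol supports neither inference: it leaves sidedness and the SD open, and at a score correlation of 0.7 a two-sided test with 27 patients has 90% power.

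The reply does not remove the point. A directional hypothesis is not a declared one-sided test. The one calculation that returns 27 without any added assumption is one-sided, and it conflicts with the non-directional ANOVA named in the same section, most plainly for the two-time-point QST measures. The alternatives need a correlation that the protocol does not give, and the three-time-point route also needs an f larger than a 0.5 SD spread over three means supports.

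**Conclusion.** The point holds as a mismatch between the sample-size basis and the planned analysis, not as a proven arithmetic error. If the test is two-sided at 5% and d refers to the SD of the change, power for the planned effect is 71% with 27 evaluable patients and 75% with all 30, against the stated 80%; full retention does not close the gap. If d refers to the SD of the score, two-sided power at 27 runs from 56% to 90% over assumed correlations of 0.3 to 0.7, so the stated 80% can be neither confirmed nor refuted. If a one-sided 5% test was meant, 27 is correct, but the named ANOVA does not carry it out.

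Severity is moderate: the study calls itself exploratory, has no control group and needs no change in enrolment.

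**What to change.** In the Statistical analysis section, state the number of sides, the test used for the calculation and the SD behind d, and quote the power that matches the planned analysis:

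- If two-sided with d on the change score: restate as 71% power with 27 evaluable patients and 75% with 30, and give the effect detectable with 80% power (d = 0.56 and 0.53).
- If one-sided 5% was intended: declare it, and analyse the primary outcome with a one-sided paired test.
- If another basis was used, such as the score SD or a three-time-point F-test: state the correlation assumed and, for the F-test, the f and the pattern of means behind it.

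The cost is one paragraph. No extra patients are needed. The downside is that the stated power may become less favourable.

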**Ethical considerations**

The study complies with the Helsinki Declaration and is submitted to the North Denmark Region Committee on Health Research Ethics for approval. The methods used have been tested and performed in several studies both in Denmark and abroad and no long-term side effects have been reported.

Patients with (OA) may eventually suffer from chronic pain leading to disabilities of the individual and associated costs for public health care systems [19]. OA is the most frequent painful musculoskeletal condition in the elderly population [26]. Recent evidence suggests that QST profiles are associated with the development of chronic pain [29,38], why studying QST profiles in patients with OA can be crucial for new pain relieving treatments.

The current study will introduce mild and short-lasting pain to the study participants but the outcome from this study can lead to a better understanding of the central nervous system, which can lead to better treatments.

The study will follow the principles of the Declaration of Helsinki and was approved by the local ethics committee of the North Denmark Region by 27/07/2016 (N-20160045). The regional data protection agency approved the project by 06/07/2016 (2008-58-0028, ID 2016-116) and registered in ClinicalTrial.Gov (NCT03389906).

Approval for this study was waived be the Danish Food and Drug Administration since gold is a primary element, not a medication, and not an implant by 10/04/2016 (LMST2016033454).

**Insurance**

The subjects are covered by the Danish Patient Insurance Association (Patienterstatningen).

**Personal data**

Data will be stored after termination of the project. These data can only be used for the interpretation of this project and will therefore not be of interest to third party. Data are stored in accordance with the stipulations in The Danish Personal Data Protection Act (Persondataloven) and other relevant Danish legislation. The project is reported to The Danish Data Protection Agency by 06/07/2016 (2008-58-0028, ID 2016-116); “Bekendtgørelse om ændring af bekendtgørelse om undtagelse fra pligten til anmeldelse af visse behandlinger, som foretages for en privat dataansvarlig”.

**Project economy**

These studies are initiated by [name], Department of Clinical Medicine, Aalborg University, and [name], Center for Neuroplasticity and Pain, Department of Health Science and technology, Aalborg University.

Department of Clinical Medicine provided funding for this study. Center for Neuroplasticity and Pain (CNAP) ([name]) provided funding for this study. CNAP is supported by the Danish National Research Foundation (DNRF121) and the Danish Rheumatism Association (R204-A7645). The Danish National Mass Spectrometry Platform for Functional Proteomics (PRO-MS; grant no. 5072-00007B); The Obelske family foundation, the Svend Andersen Foundation, and the SparNord foundation are acknowledged for grants to the analytical platform, enabling parts of this study.

**Payment to subjects**

Patients receive no payment for their participation in the study.

**Publishing of results**

The results of the project will be published in recognised journals regardless of the outcome of the project.

**Time schedule**

The experimental study will start after approval and be completed in January 2021

## Guidelines for Oral information and Informed Consent

### *Summoning Potential Subjects*

When contacting potential subjects in the outpatient clinic the following should be stated:

- That it is a request for participation in a scientific research project
- The purpose of the project
- That participation is voluntary and that the subject can withdraw from the project at any time without consequences
- That the potential subject has time to consider his/her participation before giving consent to participation in the project and that the potential subject is welcome to bring a family member or a friend to the information meeting. The potential volunteer will receive the leaflet “The Rights of a Trial Subject in a Health Scientific Research Project”/ "Forsøgspersonens rettigheder i et sundhedsvidenskabeligt forskningsprojekt" which includes information on confidentiality, right of access to documents and right to complain.
- That the material “Information for Participants”/”Deltagerinformation” will be forwarded by mail/e-mail to the potential subject in order for him/her to know more about the project before the information meeting.
- Finally, time for the information meeting is arranged

### ***The Information Meeting***

The information meeting is held in a quiet room where it is possible to have an uninterrupted conversation. Coffee/tea/soft drink may be served. The information meeting is held by a senior researcher who has been authorized to do the information.

The meeting is to include the following information/questions:

- Participation is voluntary and the subject can withdraw from the project at any time without consequences
- The subject has time to consider his/her participation before giving consent to participation in the project, and the subject is welcome to bring a family member or a friend to the information meeting.
- The subject is asked whether he/she wants a family member/friend to be present at the meeting.
- The purpose of the experiment is presented, and it is explained how the experiment is performed. The “Information for Participants”/”Deltagerinformation”, which has been sent to the potential subject in advance, is the starting point for the information meeting.
- The subject is asked if he/she is healthy or whether he/she has an infectious disease.
- The subject is asked whether he/she is a Danish citizen. If the answer is no, he/she is asked if he/she has a valid work permit.
- The leaflet “The Rights of a Trial Subject in a Health Scientific Research Project”/ "Forsøgspersonens rettigheder i et sundhedsvidenskabeligt forskningsprojekt" is handed over. It is explained that it includes information on confidentiality, right of access to documents and right to complain.
- The subject is asked whether he/she has read “Information for Participants”/ ”Deltagerinformation”. If this is not the case, we will ask the subject to read it.
- When it has been ensured that the subject has read the “Information for Participants”/”Deltagerinformation”, he/she is asked whether he/she has questions about the experiment.
- After this a demonstration is given in the lab; measuring equipment and its use is presented to the subject.
- It is underlined that participation is voluntary, and that the subject has time to consider his/her participation (please note that The National Committee on Health Research Ethics recommends 24 hours of deliberation time)
- Again, it is underlined that participation is voluntary and that the subject can withdraw his/her consent at any time without consequences.
- The subject is informed that if he/she does not need time to consider the participation, the consent can be given at the information meeting.
- Time/place for the experiment is agreed.
- Finally, information about the contact person of the experiment is given (it is shown to the subject that the name and contact details appear from the “Information for Participants”/”Deltagerinformation”) and it is informed that this person can be contacted at any time if further questions should arise.

